## Expected Duration of Participation

Youth will participate in the study for 12 months. All study visits and assessments are completed remotely. Youth can choose to complete the assessments via RedCAP survey or to have paper copies of the questionnaires sent by mail. The research coordinator will work virtually with each participant to support questionnaire completion. Completion of all questionnaires will require approximately 1 hour at each assessment timepoint. One of every three participants will be randomly selected to complete the objective behaviour measurements in addition to the questionnaires. Accelerometers will be distributed and collected by mail so that in-person visits to CHEO are not required. Participants selected for the objective measures will be required to wear an accelerometer on an elastic waistband 24 hours per day for 7 consecutive days. They will also be required to submit a screen shot of their social media screen time (app that already exists in smartphones) daily for the same 7 days. After the four assessment timepoints have been completed, youth will no longer be required to perform study activities but data collection on healthcare system impacts will continue to be collected via medical chart review for an additional 6 months. Participants randomized to the wait list control group will have access to the HELP e-intervention between the 6 and 12-month assessment timepoints.

| **Study Group** | **0 mos** | **0 to 3 mos** | **3 mos** | **3 to 6 mos** | **6 mos** | **6 to 12 mos** | **12 mos** | **12 to 18 mos** |
| --- | --- | --- | --- | --- | --- | --- | --- | --- |
| Intervention | Assess | HELP | Assess | HELP | Assess | ----- | Assess | Medical chart |
| Wait List Control | Assess | ----- | Assess | ----- | Assess | HELP | Assess | Medical chart |

Assess = completion of study questionnaires and objective measures (if applicable)
HELP = access to the HELP e-intervention with kinesiologist support
Medical chart = evaluation of mental health service use and inclusion of lifestyle behaviours in mental health service supports via medical chart review for 18 months from study enrollment

## Study Procedures/Evaluations

### Recruitment

The primary avenue for recruitment will be via 1Call1Click. During our pilot study of the HELP e-intervention (REB #21 85X) we developed a best practice advisory flag within EPIC (Appendix A) that was provided to 1Call1Click intake staff if the youth met the age criteria for the research study. Youth who access 1Call1Click have an initial assessment by intake staff. Staff have information about the research study and have been educated regarding the inclusion/exclusion criteria. If the research study could be appropriate for the patient, the intake staff will ask the patient/family if they would like more information about research. If the response is positive, intake staff will send an EPIC inbasket message to the research team who will follow up with the patient/family to discuss the study details.

During the pilot study we also received feedback from youth, families and clinicians requesting that the HELP e-intervention be more widely available to youth who are at various stages in their journey to mental wellness. Therefore, additional youth may be recruited through our two secondary recruitment options. CHEO mental health clinicians will be able to refer youth for enrollment in the research study if they have obtained permission from the youth to do so. This avenue for recruitment will enable youth on the wait list for specialist support or who are currently receiving CHEO support to be eligible for study recruitment. We will also distribute the study information via posters (Appendix B) and social media posts (Appendix C) in CHEO patient areas and through our youth partner groups (CHEO Youth Forum, CHEO-RI Family Leader Program, YouthNet / R$é$seau Ado, the study’s Lived Experience Advisory Group, etc.). Youth who contact the research team after viewing the study information will also be eligible to enroll.

### Consent

In keeping with the virtual design of the study, informed consent to participate will also be obtained electronically. Participants will be able to choose the format used to provide consent from the following options:

1. RedCAP e-consent
   RedCAP will be used to distribute the consent document, archive the complete e-consent and provide the youth with a copy of the completed consent. The researcher will verify the identity of the participant and their email address before sending the RedCAP link.
2. Verbal consent
   The researcher will connect with the participant by phone or electronically and verify their identity. The researcher will enter the participant responses during the consent discussion into RedCAP, which will automatically archive the completed consent and send a copy to the participant.
3. Paper consent
   Youth who prefer to complete a paper copy of the study consent will first speak with the researcher who will review the document, answer their questions and confirm their identity and how the consent form will be sent to the participant. The participant can choose to send/receive the paper consent form by email or regular mail.

If the patient is recruited through 1Call1Click or referral, the research coordinator will explain the study to the potential participant, including that the study materials (website, questionnaires) are only available in English at this time. The researcher will further explain that participation is voluntary and that the information will be recorded solely for research purposes and will be kept confidential. Finally, the research coordinator will explain that participation in the study will not change the mental health services available or the youth’s ability to access other services if desired. The participant will be given the opportunity to ask any questions that they wish regarding the study. Digital signatures will be acquired via RedCAP. Alternatively, participants may choose to provide a picture of a signed and dated written statement or an email confirming their consent to participate. Participants who are unable or unwilling to provide written consent have the option to provide verbal consent. All participants will receive a copy of the signed consent document.

If patients are recruited via our posters or social media posts, they will have the choice to either contact our research coordinator (and then follow the same process as for 1Call1Click described above) or to go directly to the virtual consent form on RedCap (via the published link or QR code). Informed consent will be obtained from youth able to consent for themselves (Appendix D). Youth who are unable to consent for themselves will be excluded as they are unlikely to be able to understand and/or engage independently in the HELP e-intervention. All REB-approved versions of the electronic informed consent will be archived and retained for auditing purposes. All youth who enroll in the study will be provided with the study resource document (Appendix N).

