## Exclusion Criteria

Youth will be excluded if they have an identified or suspected eating disorder because these youth often have a compulsive exercise co-morbidity that may be negatively impacted by the physical activity promoting components of the HELP e-resources. Youth will also be excluded if their health or family status is deemed to be inappropriate for the study as per their most responsible clinician.

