### HELP E-Intervention

All study participants will have access to the HELP e-intervention either immediately (HELP access between 0 and 6 months) or after a wait of 6 months (control condition, access between 6 and 12 months). The use of a wait list control is expected to decrease the impact of randomization on study recruitment and retention. Our unique HELP e-resources utilize age-appropriate graphics and interactive formats developed collaboratively with youth/parent/clinician partners. There are 4 sections: 1) Know Your Habits, 2) Physical Activity, 3) Screen Time, 4) Sleep. Know Your Habits provides youth with their personal baseline questionnaire results. Messages are tailored to each youth’s readiness for behaviour change and assessment results. Each behaviour section (physical activity, screen time, sleep) has 4 sub-sections. “Learn” conveys information linking the behaviour and youth mental health and targets youth not yet contemplating behaviour change. “Pros and Cons” targets ambivalence, supporting youth to consider the barriers/facilitators of behaviour change. “Goals” guides youth to choose from >70 step-by-step change plans. Each plan contains a sequence of 6-8 steps that youth complete to achieve their goal. Steps vary in required time (2-30 mins) and youth proceed through the steps at their preferred pace. SMART goal, overcoming road blocks and additional kinesiologist support resources are also provided. Youth can track their goals and accomplishments on the website. Access to all HELP e-modules is available to all youth but the website suggests individualized avenues for change based on each participant’s assessment results. Sample pages from the HELP e-intervention are provided in Appendix H.

Each participant will have a unique login to the HELP e-intervention (found at www.cheoactive.ca). By automatically tracking e-resource use (site visits, interactivity use, knowledge component completion), the website provides data regarding participant engagement with the intervention. These data also assess the frequency or type of e-resource use, important considerations in analyzing the intervention impact on behaviour change. Comparing initial and post-intervention questionnaire responses will indicate the potential emotional health/lifestyle behaviour change impacts of HELP e-resource access.

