### Incidental Findings

Given the nature of the study, we do not anticipate that the study will produce incidental findings. However, in the event that a patient gives any indication that there is an increased risk of harm (suicidal ideation, self-harm, harm to others) during any study contact, [name] will be notified and she will communicate directly with the most responsible clinician for the participant. [name] will identify the most responsible clinician (physician or other healthcare professional) via the EPIC and 1Call1Click records. In the event that the participant does not have an identified care provider, [name] will follow up directly with the participant. Study participants will be made aware of the limitations of confidentiality regarding the information that they disclose to the research team through the consent process.

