# Potential Risks & Benefits

## Potential Risks

There are no medical or health risks associated with participating in this study. Participants will not be required to make any changes to their health services, supports, medications or other treatments. The topics of the study (physical activity, sleep, and screen time) are not anticipated to cause harm. Discomforts during this study may occur when patients are answering questions about lifestyle behaviours that they consider or think will be viewed in a negative light. The research coordinator will reassure participants at the start of each assessment that the purpose of the questions is only to assess participants’ current behaviour so it can be compared to other study timepoints. The research coordiator will also emphasize that the research team recognizes that circumstances change regularly for all individuals. There will also be a risk to confidentiality if participants disclose information that, by law, must be reported.

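### Poster and social-media recruits can reach the consent form through a public link, which conflicts with the identity check required before the link is sent and leaves no described eligibility step on that option

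*Protocol*

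**What the plan says.** The Recruitment section of the protocol names 1Call1Click as the main source of participants and adds two secondary sources: referral by CHEO mental health clinicians, and posters or social-media posts. It describes people from the last source as youth who get in touch with the research team after seeing the material.

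The Consent section offers three formats (RedCAP e-consent, verbal, paper), each with an identity check. For e-consent: "The researcher will verify the identity of the participant and their email address before sending the RedCAP link". It then covers the explanation of the study: "If the patient is recruited through 1Call1Click or referral, the research coordinator will explain the study to the potential participant". Poster and social-media recruits are given a choice. They may contact the coordinator and follow that same process, or they may choose "to go directly to the virtual consent form on RedCap (via the published link or QR code").

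The Exclusion Criteria state: "Youth will be excluded if they have an identified or suspected eating disorder". The reason given is that the activity-promoting content could affect such youth badly. A second exclusion covers youth whose health or family status is "deemed to be inappropriate for the study as per their most responsible clinician". The Inclusion Criteria require an age of 12-17, a current link to help for emotional distress (sought, awaited or being received), ability to consent, and consent to use of the health record. The Consent section repeats that youth who cannot consent for themselves are excluded.

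**The concern.** There are two problems. The first is a contradiction: a researcher cannot verify someone before sending a link that nobody sends. Staff following the protocol would have to break one statement or the other.

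The second is an absence. The other routes put a person between the youth and the consent form, whether a trained intake worker, a clinician or the coordinator. The direct option puts nobody there, and the protocol does not say who confirms identity or applies the criteria afterwards.

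The participants are minors in distress who consent for themselves. One exclusion exists because the intervention may be harmful to a particular group, and a suspected eating disorder has to be suspected by someone. Consent also opens the medical record to review over 18 months from enrolment, so an unverified identity puts the validity of that access, and the linkage to the right record, at risk.

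**Working it through.** No arithmetic applies. The check sets the protocol's sections side by side, route by route.

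| Route | Contact before consent | Identity check before consent | Step where criteria are applied |
| --- | --- | --- | --- |
| 1Call1Click | Intake assessment, then coordinator explanation | Yes, under each consent format | Intake staff have been taught the criteria and raise research if the study might suit |
| Clinician referral | Clinician, then coordinator explanation | Yes | A clinician is in the path; no formal check described |
| Poster or post, youth contacts coordinator | Coordinator, same process as above | Yes | Coordinator contact; no formal check described |
| Poster or post, direct link or QR code | None described | None described; cannot precede a published link | None described |

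**Identity.** The e-consent rule makes verification a condition of sending the link. On the last row the link is already published, so the condition cannot be met. The Recruitment wording, which presupposes contact with the team, does not fit that row either.

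**Criteria, one at a time, on the direct option.**
- *Age and link to mental health support:* no one is assigned to confirm these. Study Assessments later asks for age, but as voluntary self-report.
- *Capacity to consent:* the rule is stated in the Consent section. What is missing is who assesses it and how, when the youth completes the form alone.
- *Eating disorder:* no person is named who could identify or suspect one.
- *Clinician judgement:* this needs a most responsible clinician. Incidental Findings provides for the opposite case: "In the event that the participant does not have an identified care provider". That contingency can arise on any route, but the direct option is the one where no professional is described as having met the youth.

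**After consent.** The next researcher contact described is in Study Assessments, where a researcher helps youth who are already called enrolled. No identity or eligibility check is assigned to that contact. The protocol does not say that signing the form triggers randomisation, and it does not describe a check between the two.

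**The case against.** The strongest reply is that consent is not enrolment. The protocol says only that a youth may open the consent form directly, and screening after consent is ordinary practice. The consent form, poster and social-media text are in appendices not shown and may contain screening questions. Later contacts would also expose many problems: the coordinator helps each participant with questionnaires, contact details and the record number are held, each participant has a unique login, and the coordinator speaks to youth 2-3 times a week early in the intervention. Undetected duplicates are therefore unlikely. Finally, the other routes are less tightly controlled than they look. Intake staff judge only whether the study might suit, referral requires only the youth's permission, and the coordinator's explanation is not described as confirming the criteria.

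Much of this stands. It rules out saying that nobody ever checks these youth, or that the other routes are fully screened. It does not remove the contradiction over the link. Self-reported screening items would not supply the researcher's identity check or a clinician's judgement, and none of the later contacts is given the task of confirming eligibility before randomisation.

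It can also be said that the second exclusion applies only when a clinician objects, so no clearance is needed. That is a fair reading, but where no clinician is identified nobody is in a position to object, and the protocol should say who decides.

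**Conclusion.** The point holds in a limited form and is a cheap improvement. The Recruitment and Consent sections cannot all be followed as written. On one of two options within a secondary recruitment route, no step before randomisation is described that verifies identity or applies the inclusion and exclusion criteria. This rests on the text shown; the appendices could narrow the gap on self-reported items.

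The number of youth affected cannot be stated. Sample Size Determination gives an enrolment rate for 1Call1Click only and no split by route.

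A reader might go further and infer any of the following, none of which the documents support:
- *That ineligible recruits would measurably weaken the trial's power.* No proportion of ineligible youth is given, only one option is affected, and any figure would rest on an invented input.
- *That credit for volunteer hours would draw in ineligible youth.* This is speculation about motive.
- *That the Potential Risks statement, "There are no medical or health risks associated with participating in this study", is part of the same defect.* It can be read as describing those who remain after the exclusion, and it has nothing to do with the consent link.
- *That giving the control group access at 6 months without renewed screening is an error.* Assessing eligibility at entry is usual, and no passage contradicts it.

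**What to change.** Reconcile the Recruitment and Consent sections as follows.

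1. Have the published link and QR code open a short contact and eligibility form instead of the consent form.
2. For every self-referred youth, require coordinator contact, the existing identity and email check, and confirmation of all Inclusion and Exclusion Criteria before the e-consent link is sent, and in any case before randomisation.
3. State which study role applies the clinician-judgement exclusion when no responsible clinician is identified. Incidental Findings already gives a study role the follow-up of such youth for safety concerns, so there is a precedent.

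The cost is one short form and one coordinator contact per self-referred youth. The contact and the identity check already exist for the other routes; explicit confirmation of each criterion would be new. The downside is slightly slower entry and possibly a few lost self-referrals. The design and the analysis are unchanged.

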### Study Assessments

A researcher blinded to study group allocation will work with enrolled youth to complete all study assessments. The accurate/reliable study questionnaires include measures of emotional strength (Strengths and Difficulties Questionnaire)^34^, lifestyle choices (Youth Quality of Life-short form)^35^, readiness for behaviour change (Stages of Change Questionnaire^36^), and sleep (Adolescent Sleep Hygiene Scale)^37^, physical activity (Habitual Activity Estimation Scale)^38^, and leisure screen time (Adolescent Sedentary Activity Questionnaire)^39^ behaviours. All enrolled youth will complete all questionnaires at 0, 3, 6 and 12 months. As in our pilot study (REB #21 85X), the questionnaires (Appendix E) will be completed virtually using RedCAP, with automated scoring of the responses according to published methods. At each assessment, youth will be asked to voluntarily self-report age (years), gender (boy, girl, unkown, other, prefer not to answer), and their use of other mental health therapies (Appendix F). Study enrollment does not restrict access to or use of other mental health supports.

The blinded researcher will also administer the objective measures of sleep, physical activity and lifestyle to a randomly selected sub-sample of participants. One in every three participants will be provided by mail with an accelerometer to wear for 7 days at the time of the 0 and 6-month assessments. Each selected youth will wear a tri-axial accelerometer (Actigraph GT9X-BT, 180 day memory) on a waist-worn belt, over the right hip, in the mid axillary line, 24 hours/day for 7 days^40^ in addition to completing the study questionnaires. The goal is 24 hour accelerometer wear for 7 consecutive days to capture both physical activity and sleep, and to minimize data loss (monitor forgotten, etc.). The Actigraph GT9X-BT ([www.theactigraph.com](http://www.theactigraph.com)) can be worn for swimming or bathing to a 1-metre depth. Sleep times and reasons for device removal will be recorded on a log sheet (Appendix G). A minimum of 10 hours of wear time per day during waking hours will be required so that established cut points^41^ can be used to calculate daily minutes of sedentary, light and moderate+vigorous activity. The ActiLife software (Version 6.13.5, Actigraph Inc.) also calculates sleep duration based on measurement epochs lacking movement. At least 3 weekdays and 1 weekend day of valid data will be required. Screen use will be measured by utilizing the social media tracking function in the smartphone owned by each participant^42^. The researcher will explain to each participant how to access the social media tracking function that is build into their smartphone. Participants will be asked to take a screen shot of their social media use each day at the time they go to bed and to share the screen shot with the research team. Participants who do not own a smartphone will not complete the objective measures of lifestyle behaviours.

The research coordinator will collect the healthcare system impact outcomes via medical chart review after participants have completed the 12-month assessment. For the 18 months after study enrollment, we will record the number and type of youth mental healthcare system contacts (request for support, appointment scheduling, treatment visit). We will also track the number, type (e.g., community provider, peer support, outpatient, day treatment, inpatient), purpose (assessment, counselling), professional seen (e.g., psychiatrist, psychologist, social worker, nurse) and length (visit length in minutes) information for each service delivery visit (i.e., appointments/visits with any type of mental healthcare service provider). Health record notes for all mental healthcare visits will be reviewed in detail to identify all content related to sleep, physical activity or screen time assessments, discussions or recommendations for change. The complete text of each lifestyle-related clinic note will be de-identified for any patient-specific information before being transferred to our research database. Sex and mental health diagnoses will also be extracted from health records.

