In our pilot study, youth who engaged with the HELP e-intervention demonstrated positive changes to emotional well-being and lifestyle behaviours. However, initiating routine engagement with the intervention was a struggle for a majority of participants. To facilitate their engagement into the study, the research coordinator will directly engage with enrolled youth 2-3 times/week until they are independently able to implement the intervention. Regular contacts with the research coordinator (via telephone, zoom or Facetime as per participant preference, Appendix I) throughout the 6-month intervention will support youth to engage with the intervention activities. The extent of this support provided to each participant will be tracked (# of sessions, length and content of each session).

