### Types of data (direct or indirect identifiers)

This study will utilize identifiable information. *Directly identifying information* (name, phone number, email) will be recorded to facilitate participant follow up and support. The research coordinator will utilize this information to deliver the intervention and schedule the study assessment visits. The indirectly identifying informaiton will be the EPIC MRN, which will be used to retrospectively gather the healthsystem impact outcomes.

*All other study information* (e.g., data captured on data collection tools, website tracking) *will be de-identified.* Direct and indirect identifiers will be removed and replaced with a unique ID code for each participant. The principal investigator will retain a master list that links the participants’ code with their directly identifying information so data can be re-linked if necessary.

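### The statement that a blinded researcher completes all assessments is contradicted by the protocol's own role assignments: the coordinator who coaches HELP youth also supports the questionnaires

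*Protocol*

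**What the plan says.** The blinding statement is in *Study Assessments*: "A researcher blinded to study group allocation will work with enrolled youth to complete all study assessments". The same section extends it to the accelerometer and smartphone sub-study: "The blinded researcher will also administer the objective measures of sleep, physical activity and lifestyle to a randomly selected sub-sample of participants".

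Other sections describe the research coordinator's work:

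- *Expected Duration of Participation*: "The research coordinator will work virtually with each participant to support questionnaire completion".
- *Potential Risks*: "The research coordinator will reassure participants at the start of each assessment".
- *HELP E-Intervention*: "the research coordinator will directly engage with enrolled youth 2-3 times/week until they are independently able to implement the intervention", with regular contacts after that for the rest of the 6 months.
- *Types of data (direct or indirect identifiers)*: "The research coordinator will utilize this information to deliver the intervention and schedule the study assessment visits".
- *Study Assessments*, on the healthcare outcomes: "The research coordinator will collect the healthcare system impact outcomes via medical chart review".

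*Study data* adds that one contact form (Appendix I) standardises the notes of both support sessions and assessments. *HELP E-Intervention* cites that same appendix for the coordinator's coaching contacts.

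**The concern.** A blinded assessor cannot also be the person who coaches one arm. If staff follow *Expected Duration of Participation* and *Potential Risks* as written, a youth in the immediate-access arm is helped through the questionnaires by the person who has been encouraging them to sleep more, move more and use screens less. A wait-list youth is helped by someone with whom they have no coaching relationship yet.

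The primary outcome and the main behaviour outcomes are self-reports, and staff help is a deliberate part of collecting them: *Summary of Work to Date* reports that most interested youth who did not enrol in the pilot found the questionnaires daunting without researcher support. *Potential Risks* itself expects discomfort over behaviours that youth think will be judged badly. A wish to please one's coach would act mainly in one arm and in the direction of efficacy. It could not be removed once the answers are recorded.

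**Working it through.** No arithmetic applies. The check is whether one set of staff roles can satisfy every section at once.

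**Step 1. Who does what.**

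| Task | Role named | Section |
| --- | --- | --- |
| Works with youth on all assessments | Blinded researcher | Study Assessments |
| Objective measures | Blinded researcher | Study Assessments |
| Supports questionnaires with each participant | Research coordinator | Expected Duration of Participation |
| Speaks to youth as each assessment begins | Research coordinator | Potential Risks |
| Coaches youth during HELP access | Research coordinator | HELP E-Intervention |
| Delivers HELP and schedules assessments | Research coordinator | Types of data |
| Extracts chart outcomes | Research coordinator | Study Assessments |

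The third and fourth rows assign to the coordinator work that the first row assigns to the blinded researcher.

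**Step 2. Can the coordinator be the blinded researcher?** The schedule table in *Expected Duration of Participation* gives the knowledge that coaching conveys at each assessment:

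- 0 months: no one has been coached, so coaching reveals nothing.
- 3 and 6 months: only the immediate-access arm has been coached. Whoever coaches knows the arm.
- 12 months: both arms have been coached, at different times, and only the wait-list arm recently. The coach still knows who was in which arm.

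So the coordinator cannot be blind at 3, 6 or 12 months. *Efficacy Outcomes* places the primary SDQ comparison at baseline to 6 months. It also uses the wait-list arm's 6-to-12-month change as evidence of efficacy, and that period too ends in an assessment supported by the coach.

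**Step 3. Is a separate assessor defined elsewhere?** *Additional Support* mentions a research assistant, but only for the Safety Plan, and gives that role no assessment duty. No section separates coaching from assessing or says the coordinator is kept blind. The shared Appendix I form points the other way: even a separate assessor who used it might see coaching notes.

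**Step 4. Could the coaching be someone else's job?** The study schedule refers to kinesiologist support, which might suggest a different person. But *Study data* calls Appendix I the kinesiology support form, and *HELP E-Intervention* cites Appendix I for the coordinator's contacts. On the protocol's own cross-references these are the same contacts.

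**Result.** The sections cannot all be followed with the blind intact.

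**The case against.** The strongest reply is that this is loose drafting. *Study Assessments* names a blinded researcher twice, the team has more than one role, and the two conflicting sentences sit in a logistics section and a risk paragraph. That is plausible, and it limits the point. A reader might infer that the claimed blinding does not exist at all, and the document does not show that: a separate assessor may well be intended. What stands is that staff who follow the text as written would break the blind, which is reason enough to correct it.

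Second, youth may answer by online survey or on mailed paper, support is virtual, and scoring is automated. The protocol does not say the coach watches the answers being given. Automated scoring removes bias in scoring, but not in answers given with help.

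Third, youth know their arm in a wait-list design, so reporting bias remains even with a fully blinded helper. This stands in full. Separating the roles removes one avoidable layer of bias, not all of it.

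Fourth, a reader might count the coordinator's chart review as part of the contradiction. It is not: the protocol claims no blinding there. Counts, visit length and professional seen are largely matters of record. *Healthcare System Outcomes* applies an existing coding framework and has two team members analyse the qualitative data independently. Judgement enters mainly in identifying lifestyle content in the notes.

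Finally, it is tempting to turn an assumed SDQ shift into an inflated error rate. The protocol gives no SDQ standard deviation and no basis for choosing a shift, so the result would only restate the assumption.

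**Conclusion.** The point holds as an internal contradiction. The blinding promised for all assessments is incompatible with the tasks given to the research coordinator, who would know allocation at the 3- and 6-month assessments, including the primary SDQ comparison. The likely direction of bias favours HELP; its size is not estimable from the document. The direction rests on two assumptions: that the coordinator's help has some influence on answers, and that youth answer more favourably to someone who has coached them. The contradiction itself needs neither. The baseline assessment need not be affected. Chart extraction is a separate and lesser matter.

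**What to change.** 1. Amend *Expected Duration of Participation* and *Potential Risks* so that the blinded researcher named in *Study Assessments* opens and supports every assessment session, and state that this is a different person from the coordinator.
2. Limit the coordinator's contact with participants to recruitment, consent, scheduling and HELP support.
3. Keep assessment records separate from the coaching contact form (*Study data*, Appendix I), so that the assessor does not see coaching notes.
4. Have the assessor ask youth at the start of each session not to reveal their group.
5. If the roles cannot be separated, withdraw the blinding statement and report the assessments as unblinded.

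Report in either case that participants knew their arm.

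The cost is mainly rewording and a transfer of tasks. The session time is already planned: with roughly 100 to 200 enrolled, four assessments and about 1 hour each, at most 100 × 4 × 1 = 400 to 200 × 4 × 1 = 800 hours before dropout. If the blinded researcher already exists as a separate person, no new staff are needed. If not, part of that time has to be found elsewhere, or item 5 applies.

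As a separate suggestion, code the extracted lifestyle notes without arm or website-use fields. They are de-identified before entering the research database, so this adds little work and does not require moving the chart review to another role.
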